### Ethical Considerations

On consultation with and review from the local Research and Innovation team, it was decided that because this study is a service evaluation, ethics approval is not required [22]. This was confirmed using the Human Research Authority Research Decision Tool [23]. Explicit patient consent was also deemed unnecessary, as researchers were considered to be members of the direct clinical care team. The lack of participants means that compensation disclosure does not apply. Additionally, this protocol prioritizes minimizing disruption to the clinical diagnostic pathway and interfering with patient care. Using a preexisting IT infrastructure and conducting our analysis outside of the direct specimen pathway, we help to limit any disturbance to the clinical service provided by the pathology department. Moreover, using a separate dedicated PC, we prevent the CBT’s interference with the reporting system and subsequently patient care. This is enhanced by the fact that connections between the WSIs to be analyzed and the patient are removed before the CBT is applied. This is especially important in the advent of discordant results between the CBT and the current standard of care.

With regard to patient confidentiality, only necessary patient identifiable data will be collected and then deleted at the earliest opportunity. In fact, NHS numbers are only collected to facilitate honoring patients’ choices with regard to the NDOS check. This process is necessary to allow patients’ opt-out wishes to be respected and upheld. The specimen numbers facilitate the collection of data from the corresponding pathology reports, and these are Trust-specific. From this point, all data collected will be anonymized. The WSIs are also anonymized at the time of extraction, with an additional quality control check put in place. Furthermore, access to the data and WSIs collected as part of this service evaluation will be restricted to the research team.

In this vein, another consideration throughout this design is data security. WSIs for the service evaluation will be kept on the NHS Trust secure servers in a dedicated folder and subfolders. Their transfer to the dedicated CBT workstation will be enabled by an encrypted hard drive, which will be stored securely on Trust premises. As mentioned previously, all images will be deleted from the hard drive after the CBT analysis is complete. The other data collected (including NHS numbers) will be stored on the Trust’s Microsoft OneDrive system, with access restricted to the research team. When transferring NHS numbers to R-DIT for NDOS checks, a secure NHS email will be used.

## Results

The study started in April 2025. There are no results to present to date, as this paper is focused on study design, and final results have yet to be generated. As of March 2026, 366 potentially analyzable cases have been collected, and the anticipated end date is May 2026. This study will be considered complete once the target 400 cases have been analyzed. Given the prospective nature of this study, the duration/achieving this target will depend on the variability of routine clinical throughput. The results of this evaluation will be the subject of a separate publication in which any deviation from this protocol will be described, as appropriate.

## Discussion

### The Protocol in a Wider Context

This protocol details a clinical service evaluation for validating the ability of a diagnostic CBT within a digital pathology workflow. To the best of our knowledge, no CBT has been approved by the National Institute for Health and Care Excellence (NICE) for use within digital pathology. In fact, a NICE medtech innovation briefing on Paige Prostate published in 2021 highlighted the absence of prospective, UK-based evidence [24]. General comments provided by experts read that “prospective use and audits would be important to inform how valuable the technology could be in practice,” and the document referenced the Oxford-based project as a “recent and ongoing” study. This protocol sets out such a study in the BC field. It is sufficiently flexible to be adapted to ever-evolving diagnostic parameters in clinical practice as well as ongoing updates to technologies. Clinical service evaluations after such updates are critical to ensuring that high levels of performance are maintained in the face of changes, for example, when the definitions of HER2 status were updated in 2023 in the United Kingdom to incorporate the emergence of HER2-low BCs [25].

Consideration should be given to what the next steps may be from a service evaluation such as this to full clinical adoption. Given the different digital infrastructures within NHS Trusts across the United Kingdom, service evaluations should be conducted for any given technology within each specific Trust considering its adoption. Such individualized assessments will not only allow each Trust to see whether the technology performs well within their systems and for their patients, but also contribute to the overall strength of evidence behind the technology. Building on this, one of the next steps would be to trial the effect of the technology directly on patient care. Ideally, this would take the form of a randomized controlled trial comparing groups who had CBT involved in their treatment pathway and those who did not.

Another key step to galvanize clinical adoption of CBTs within pathology is NICE approval. NICE produces technology appraisal guidance where the recommendations are based on “a review of clinical evidence and cost effectiveness” [26]. The manual for NICE health technology evaluations is extensive and states that “NICE considers all types of evidence in its evaluations” [27]. The authors of this manual explain that for “diagnostic technologies,” “end-to-end studies” are preferred, and “diagnostic accuracy studies” are also included in this document. A study such as ours could help provide essential information for these health technology evaluations and inform NICE recommendations.

As mentioned, for recommended technologies, NICE assesses information regarding cost-effectiveness, where it is asked, “does it represent value for money?” [26]. Its manual details a specified “reference case” that defines the methods for economic evaluation that NICE prefers [27]. Within this, they include cost-utility and cost-comparison analyses. To this end, a health economics evaluation in line with our study protocol has been considered. This evaluation would directly compare the cost of processing breast biopsies for ER, PR, and HER2 testing using the current standard of care (ie, immunohistochemistry with or without ISH) versus replacing it with a CBT (ie, without immunohistochemistry with or without ISH). To determine the resources used by the current diagnostic pathway within the LTHT laboratory, estimates will be taken directly from the existing standard of care used. This will include resources used for slide preparation; pathologist slide review and reporting time; costs of laboratory staffing, reagents, and equipment; costs of ancillary investigations for ER, PR, and HER2; and the costs of physical and electronic slide storage. These would then be directly compared to the costs of the CBT. This would include the time stamps collected in this study, covering the time taken by the CBT to analyze images and produce results, and the costs to the NHS of accessing the CBT reports. The estimation of the potential savings from the use of the CBT will include both straightforward and more complicated analyses. For directly comparable parameters, such as the cost of testing, the difference would be estimated. For parameters such as the potential savings of freeing up pathologists’ time in slide review for other uses, modeling will be used to estimate these scenarios. The wealth of information this evaluation could bring will again help inform the Trust of the CBT’s usefulness as well as provide evidence to NICE for a technology appraisal.

Finally, it would be beneficial to align a service evaluation such as ours with a degree of usability testing. It has been found from questioning pathology consultants in the United Kingdom that for acceptance of an AI tool, “high levels of usability” are key [28]. Moreover, King et al [28] found that their results “suggested an iterative design process with early user involvement” would help promote “AI uptake”. Usability testing is planned to accompany this service evaluation design. Separately, pathology trainees and consultants will be able to view and interact with the CBT, using it as intended but not on ‘live cases’. This will give the users a chance to explore the technology without any concern of error or interruption of normal care. Feedback from this testing will be gathered and used to help perfect the interface of the CBT.

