### Data Analysis

To validate the CBT’s diagnostic accuracy in this clinical service evaluation, concordance will be established with the ground truth (ie, the pathology report). Measures including sensitivity; specificity; false-positive rates and false-negative rates; and positive and negative predictive values for ER, PR, and HER2 will be calculated based on the formulae presented in Table 1. The time difference between the 2 time stamps collected will also be calculated. From this, a range and median time for the CBT’s result generation will be quantified.

**Table 1 table1:** The standard diagnostic metrics used to measure the performance of PANProfiler Breast.

Performance metric	Definition
Concordance	Number of concordant cases/total number of cases with definitive PANProfiler result
Sensitivity	TP^a^/TP+FN^b^
Specificity^c,d^	TN^c^/TN_FP^d^
Positive predictive value	TP/TP+FP
Negative predictive value	TN/TN+FN
False-negative rate	FN/TP+FN
False-positive rate	FP/TN+FP
Test replacement rate	Number of cases with definitive PANProfiler result^e^/total number of cases
Complete test replacement rate	Number of cases with definitive PANProfiler results*for all marks/total number of cases

^a^TP: true positive.

^b^FN: false negative.

^c^TN: true negative.

^d^FP: false positive.

^e^Definitive PANProfiler result for HER2 is “negative,” and definitive PANProfiler result for estrogen receptor or progesterone receptor is “positive” or “negative.” The table is taken from the supplementary material of our previous publication [21].

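### The sketched cost comparison leaves all conventional testing out of the CBT arm, although Table 1 treats replacement as partial; as written, the test-cost saving is overstated

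*Protocol article*

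**What the plan says.** The economic comparison is described in the Discussion, under The Protocol in a Wider Context. One arm is costed "using the current standard of care (ie, immunohistochemistry with or without ISH"). The other is described as "versus replacing it with a CBT (ie, without immunohistochemistry with or without ISH"). The inputs named for the CBT arm are the study's time stamps, "covering the time taken by the CBT to analyze images and produce results, and the costs to the NHS of accessing the CBT reports". On the saving itself the text says: "For directly comparable parameters, such as the cost of testing, the difference would be estimated". Modeling is mentioned for parameters such as freed pathologist time. Neither replacement rate is mentioned in that paragraph, nor is any cost for tests that remain.

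Table 1 (Methods, Data Analysis) defines the test replacement rate with the "number of cases with definitive PANProfiler result" as numerator and all cases as denominator. It adds a "Complete test replacement rate", which requires definitive results for all markers. Footnote e limits what counts: "Definitive PANProfiler result for HER2 is “negative", whereas for ER and PR either a positive or a negative output is definitive.

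The Introduction states that every newly diagnosed invasive breast cancer in the United Kingdom is tested for ER, PR and HER2.

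**The concern.** The two parts of the article describe different uses of the device. Table 1 has replacement rates because some cases will not receive a definitive result. The cost comparison describes a pathway in which no case has a conventional test. If the comparison is carried out as described, it credits the CBT with the cost of tests that would still be done, while the CBT itself is paid for on every case.

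The gap is structural for HER2. Because only a negative output is definitive, a HER2-positive tumour can count as replaced only if the CBT wrongly calls it negative. The better the device is at not missing HER2-positive disease, the further HER2 replacement must fall below 100%.

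The evaluation is meant to help inform the Trust and to supply evidence for a NICE appraisal, and the article offers its design as a blueprint for other departments. The bias favours the device, and a reader of the resulting cost figure would not see it.

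**Working it through.** The article states no cost, saving or replacement rate, so there is no figure of its own to reproduce. The check is algebraic, with assumed values for illustration.

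**Inputs from the article**
- CBT arm: no immunohistochemistry and no ISH (Discussion).
- Saving on the cost of testing: a plain difference between arms (Discussion).
- r, the test replacement rate for a marker: definitive results divided by all cases (Table 1). No value is given.
- HER2: only negative is definitive (Table 1, footnote e).
- Target number of cases: 400 (Identification of Cases; Results).

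**Inferred:** a case without a definitive result for a marker still has that marker's conventional test. Table 1 does not say this in words. It follows from the name and definition of the metric and from the Introduction's statement that all three markers are tested in every newly diagnosed invasive cancer.

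**Formulas, per case and marker.** Let T be the mean conventional test cost and C the CBT cost.
- Saving as written: T − C.
- Saving with remaining tests counted: T − [C + (1 − r)T] = rT − C.
- Overstatement: (T − C) − (rT − C) = (1 − r)T.

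C cancels, so the absolute overstatement does not depend on the price of the CBT. It is above zero whenever r < 1. Over the three markers it is the sum of (1 − r)T, each marker with its own r and T.

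**Illustration.** r and C = 0.3T are assumptions.

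| r | Tests remaining, of 400 | Overstatement | Saving as written | Saving with remaining tests |
|---|---|---|---|---|
| 0.9 | 0.1 × 400 = 40 | 0.10T | 0.70T | 0.9T − 0.3T = 0.60T |
| 0.7 | 0.3 × 400 = 120 | 0.30T | 0.70T | 0.7T − 0.3T = 0.40T |
| 0.5 | 0.5 × 400 = 200 | 0.50T | 0.70T | 0.5T − 0.3T = 0.20T |

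**Ceiling for HER2.** Let p be the HER2-positive share. With no false-negative HER2 results, only HER2-negative cases can be definitive, so r is at most 1 − p. For assumed p of 5%, 10%, 15% and 20%, r is at most 0.95, 0.90, 0.85 and 0.80. That leaves at least 20, 40, 60 and 80 of 400 HER2 tests. r = 1 for HER2 would require the CBT to call every case negative.

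**The case against.** The strongest reply is that this is not part of the study's analysis. The Data Analysis section contains no economic component. The Discussion says only that such an evaluation has been considered, writes much of it in the conditional, and the Conclusions list it as further work. No accuracy result depends on it, and a fuller economic plan that is not shown could add the remaining tests. This stands as a limit on the importance of the point, and it means that no reported saving can be called wrong. It does not remove the conflict: the article states a comparator, and that comparator disagrees with its own Table 1.

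A second reply is that the sentence only names two testing routes to be costed and later weighted by the replacement rates, since the cost lists are not exhaustive and more complicated analyses are promised. The text does not say this. It gives freed pathologist time as the example for modeling, places the cost of testing under the simple difference, and never links the replacement rates to the costing.

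Three stronger readings are tempting and are not supported:
- A reader might divide by the complete test replacement rate and conclude that savings are inflated by a factor of 1/r. That counts no saving for a case that is definitive for ER and PR but not for HER2, although two of its three tests would be avoided. The marker-specific rates are the right weights.
- A reader might conclude that full replacement is impossible for this device. The article does not describe its full HER2 output or indications for use and refers elsewhere for the detail.
- A reader might argue that a negative HER2 output replaces nothing now that HER2-low is recognised. The article mentions HER2-low only as an example of a change after which evaluations should be repeated ("when the definitions of HER2 status were updated in 2023 in the United Kingdom to incorporate the emergence of HER2-low BCs"). It does not say whether the device separates that category.

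**Conclusion.** The point holds for the comparison as written. The CBT arm omits conventional testing that Table 1 implies will remain, and the test-cost saving for each marker is overstated by (1 − r) × test cost. The direction follows from the article's definitions together with the inference that cases without a definitive result are still tested. For HER2 the overstatement can be zero only if every case is called negative.

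The size cannot be derived from the article. The 10% to 50% of test cost shown above rests on assumed r between 0.9 and 0.5, and the HER2 ceilings on an assumed positive share of 5% to 20%. The formula also takes the mean test cost to be the same in replaced and remaining cases. That may not hold for HER2, where ISH is used in only some cases.

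The weight is moderate: the comparison should be corrected before the evaluation is run or copied elsewhere. A reader might infer that the study's results are compromised; they are not, because sensitivity, specificity and the other Table 1 measures do not use the cost comparison.

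**What to change.** Define the CBT arm, for costing purposes, as the CBT on every case plus conventional testing for each marker without a definitive result. Take the marker-specific test replacement rates from this study and carry their confidence intervals into the cost difference. Keep full replacement only as a scenario labelled as an upper bound.

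This needs a few changed sentences in the Discussion and one revised model arm. It needs no new data, because Table 1 already requires the replacement rates. The price is a less favourable projected saving.

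A scenario in which a negative HER2 output does not replace testing because HER2-low must be reported is optional, and sensible only if the HER2 score and any ISH result were already recorded. Collecting them retrospectively should not be assumed feasible: specimen numbers are deleted once the report data are taken, and 366 potentially analyzable cases had been collected by March 2026.

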### Limitations

As discussed by Colling et al [19] in their clinical practice road map, there are inherent issues with establishing a ground truth for some AI technologies. They describe that using a pathologist’s microscopic assessment as the ground truth is a “controversial assumption”. This is due to the interobserver variability seen and the subjective nature of the assessments. They suggest that validation is normally needed across multiple pathologists and laboratories. As our study design mimics the standard clinical pathway, it will solely rely on pathologists’ assessment of the case for ER, PR, and HER2 status. While this does not necessarily mitigate the issues highlighted, it would compromise the aim of this study to assess the CBT’s utility in a real-life clinical environment. To address this limitation, it may be necessary to carry out additional testing in a specific investigation. Additionally, as mentioned earlier, this protocol may not precisely fit within the infrastructure of other NHS Trusts. This lack of complete generalizability is unavoidable and is not wholly a limitation, as others can adapt this protocol to fit the needs of their departments, pathologists, and patients. While this protocol can be adapted to other Trusts, it is important to note that it does not assess the integration of a technology into a specific workflow. This has been deliberate, given that the focus of this design was to mitigate the premature integration of a newly developed and yet clinically unproven diagnostic technology. From a broader perspective, the foundations of this service evaluation could be implemented in health care systems outside the UK. With that said, as is the case for other United Kingdom sites, there will be logistical, regulatory, and clinical hurdles specific to each individual administration. For example, the NDOS appears to be NHS England specific [20] and would likely not need to be considered internationally. How the evaluation’s foundations may apply in other international diagnostic histopathology services is beyond the scope of this paper.

### Conclusions

The use of CBTs and AI within pathology in the United Kingdom is increasingly imminent. To validate and determine which technologies will perform best within a real-life clinical environment, clinical service evaluations, such as the one we have designed, are warranted. This protocol can provide a blueprint for other researchers and other pathology departments to enable their own evaluations. It may also provide the basis for further work needed, such as health economics evaluations and usability testing.

## Abbreviations

AI: artificial intelligence
BC: breast cancer
CBT: computer-based technology
ER: estrogen receptor
H&E: hematoxylin and eosin
HER2: human epidermal growth factor receptor-2
ISH: in situ hybridization
LIMS: laboratory information management system
LTHT: Leeds Teaching Hospitals National Health Service Trust
NDOS: National Data Opt-Out Scheme
NHS: National Health Service
NICE: National Institute for Health and Care Excellence
PR: progesterone receptor
R-DIT: Research Data and Informatics Team
UKCA: UK Conformity Assessed
WSI: whole slide image
